### Randomisation

The random allocation has been stratified by school. An epidemiologist away from the study site generated the allocation schedule in Excel using the *rand between* function, using block randomisation with variable block sizes. Two pre-printed adhesive labels were placed in opaque envelopes, which were sealed and stamped in London and Bangalore by persons not involved in the trial. For each child recruited, the optometrist opens the next envelope in sequence to see to which arm of the trial the child has been allocated. One label has the unique study ID number and code for ready-made spectacles or custom spectacles which is adhered to the child’s data collection form. The other label, which only has the unique study ID, is adhered to the red card issued to the child.

### Primary outcome

The primary outcome is the proportion of children who are wearing their spectacles at an unannounced visit to the school 3 to 4 months after delivery of the spectacles. A field worker, masked to the allocation arm, assesses spectacle wear using categories described by Wedner [13]. Categories 1 or 2 below are used to define spectacle wearing, and categories 3 or 4 as non-spectacle wearing:wearing the spectacles at the time of the unannounced visitnot wearing the spectacles at the time of the visit but have them at schoolnot wearing the spectacles at the time of the visit but said they are at homenot wearing the spectacles at the time of the visit as they are broken or lost

Children categorised as non-spectacle wearing are given an opportunity to give two reasons. The field worker asks the child the reason and this is coded and recorded on the follow-up data collection form.

Fieldwork has been planned such that the initial assessment, delivery of spectacles and follow-up 3 to 4 months later do not coincide with school examination periods, long school holidays, or the end of the school year when children may leave school.

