#### Primary analysis

The proportion of children wearing or having their spectacles with them at school at 3 to 4 months will be compared between the intervention and comparator arms, using the risk difference with 95 % confidence intervals.

We will also calculate and present the risk ratio with 95 % confidence intervals.

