#### Additional analyses

(i)*Reasons for non-spectacle wear*Reasons for non-wear will be compared in children who were not wearing ready-made spectacles or custom spectacles.(ii)*Predictors for spectacle wear*We will investigate factors that may affect spectacle wear in this cohort such as gender, age, degree of uncorrected refractive error in the better seeing eye, previously wore spectacles, and parental spectacle wear using multivariable logistic regression analysis.

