### Harm

Inaccurate prescribing or fitting of spectacles can cause blurred vision and/or symptoms of eyestrain or headache whilst the spectacles are worn. All refractions in this trial will be undertaken by highly experienced optometrists, and so inaccurate prescribing is highly unlikely. In addition, children who have refractive errors not suitable for ready-made spectacles will not be eligible for the trial, thus reducing the risk of symptoms arising through under/over correction.

Children will not be specifically asked whether they have these symptoms but will be offered the opportunity to say whether symptoms were the reason why they discontinued wearing spectacles at the time of the unannounced follow-up visit. Any child who says that blurred vision, eyestrain or headaches were why they did not wear their spectacles will be refracted again and given a new pair of spectacles, if required.

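### The outcome labelled spectacle wear also counts children who only have their spectacles at school, so it could mask a deficit in observed wear, and the reason question may miss these children

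*Protocol article*

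**What the plan says.** The Primary outcome section of the protocol article opens with a measure of observed wear: "The primary outcome is the proportion of children who are wearing their spectacles at an unannounced visit to the school". It then lists four categories and sets the rule: "Categories 1 or 2 below are used to define spectacle wearing, and categories 3 or 4 as non-spectacle wearing". Category 1 is a child seen wearing the spectacles. Category 2 is a child seen without them who has them at school. Category 3 is a child who says they are at home, and category 4 a child whose spectacles are lost or broken.

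The Primary analysis section uses the same composite: "The proportion of children wearing or having their spectacles with them at school at 3 to 4 months will be compared", by risk difference with a 95% confidence interval. The margin in the Sample size calculation section is 10 percentage points.

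Three places deal with reasons and symptoms:

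- Primary outcome: "Children categorised as non-spectacle wearing are given an opportunity to give two reasons".
- Additional analyses: "Reasons for non-wear will be compared in children who were not wearing ready-made spectacles or custom spectacles".
- Harm: "Children will not be specifically asked whether they have these symptoms"; instead they are "offered the opportunity to say whether symptoms were the reason why they discontinued wearing spectacles at the time of the unannounced follow-up visit". A child who gives such a reason is to be refracted again.

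**The concern.** The Purpose, the hypothesis and the Discussion all speak of wear. The Methods/design rationale also treats acceptance of ready-made spectacles as something measured by wear. What is analysed is wear or possession at school.

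The difference could matter in this comparison. Eligibility criterion (c) admits children whose acuity with the spherical equivalent is up to one line worse than with full correction, and ready-made lenses leave astigmatism uncorrected. The Background lists lack of perceived benefit among reasons for not wearing spectacles. A child who brings the spectacles to school but does not use them is a plausible form of failure, and the rule scores that child as a success. In a non-inferiority trial, a shift of this kind pulls the composite difference towards zero, which favours the conclusion being tested. That conclusion also decides whether the cost-savings analysis is done.

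The same child may be lost to the symptom record. On the Primary outcome section as written, a child who carries the spectacles but leaves them off because of blur or headache is classed as a wearer and is not offered the reason question. No later analysis can recover an answer that was not collected.

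**Working it through.** **1. What the plan's own figure can tell us.** The article states 240–260 per arm, one-sided, significance level 0.05, 90% power and a 10-point margin, but no expected wear rate. With equal true rates p, n per arm = 2p(1−p)(z₁₋α + z₀.₉₀)²/0.10².

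- One-sided 0.05: n = 264 at p = 81%, 253 at 82% and 242 at 83%. The stated range therefore fits about 81–83% (or the mirror values, 17–19%).
- One-sided 0.025: n = 254 at 86% and 238 at 87%.
- At p = 50%, n would be 429 (one-sided 0.05) or 526 (one-sided 0.025).

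The stated size can be solved backwards for a total rate. It says nothing about how that rate divides between categories 1 and 2, so it neither supports nor refutes the concern.

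**2. Could the composite mask a deficit?** The category rates below are assumptions, because the article gives none. Custom arm: category 1 = 50%, category 2 = 30%, composite 80%. Ready-made arm: category 1 = 35%, a deficit of 15 points. A fraction f of the displaced 15 points goes to category 2 and the rest to categories 3 and 4. Take n = 460/2 = 230 per arm (Trial status) and margin 0.10.

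P(non-inferiority) = Φ((0.10 − (pC − pR))/SE − z₁₋α), with SE = √(pC(1−pC)/n + pR(1−pR)/n).

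For f = 1: pC = pR = 0.80, SE = √(2 × 0.16/230) = 0.0373, and 0.10/0.0373 − 1.96 = 0.72, giving 0.765.

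| Outcome | Custom v ready-made | 95% CI (one-sided 0.025) | One-sided 0.05 |
|---|---|---|---|
| Composite, f = 1 | 80% v 80% | 0.765 | 0.85 |
| Composite, f = 0.75 | 80% v 76.25% | 0.37 | 0.49 |
| Composite, f = 0.5 | 80% v 72.5% | 0.09 | 0.16 |
| Composite, f = 0 | 80% v 65% | 0.001 | 0.002 |
| Category 1 alone | 50% v 35% | 0.001 | 0.003 |

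Masking is strong only when nearly all displaced children carry their spectacles. At f = 0 the composite shows the full 15-point deficit. If ready-made spectacles instead lowered carrying while wearing was unchanged, the composite difference would be wider than the category 1 difference.

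**3. Precision of category 1 alone.** At an assumed 50% in both arms, SE = √(2 × 0.25/230) = 0.0466 and the 95% half-width is 1.96 × 0.0466 = 0.091, about ±9 points. With truly equal arms, the chance of meeting the margin is Φ(0.10/0.0466 − 1.96) = 0.57, or 0.69 at one-sided 0.05.

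**4. Who is offered the reason question.** Setting the three sections side by side:

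- Primary outcome: children categorised as non-wearing. Under the scoring rule that is categories 3 and 4.
- Additional analyses: children who were not wearing. Read literally this could include category 2; read with the scoring rule it does not.
- Harm: children who stopped wearing, with no reference to the categories.

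The first excludes category 2. The other two leave it open.

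**The case against.** The strongest case on the other side has five parts.

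- **The definition is open.** The scoring rule follows directly on the naming of the outcome, is attributed to a published classification, is applied by a masked field worker and is restated in the Primary analysis section. This stands. A reader might infer a concealed or shifting endpoint; the article does not support that.
- **Bias towards non-inferiority is not shown.** A reader might infer that counting category 2 favours ready-made spectacles. That holds only if displaced children fall mainly in category 2, and nothing in the article says so. A single-moment reading is also noisy, since a regular wearer may have the spectacles off at that instant. Equal misclassification of that kind in both arms also pulls a category 1 difference towards zero, so category 1 is not clearly the more sensitive outcome. The trial cited in the Background, where self-reported but not observed wear rose, is no support: category 2 is worded as having the spectacles at school, and the category that rests on the child's word (at home) counts as failure.
- **A supportive analysis may be planned elsewhere.** The article condenses a fuller plan and the SAP is not shown, so the absence of a category 1 analysis is not itself a fault.
- **Category 2 children may be asked after all.** A reader might infer that they never are. That rests on the Primary outcome section alone; the other two sections do not clearly exclude them. Acuity with the new spectacles is also measured at delivery, which is an earlier check on blur, though it precedes any eyestrain or headache from use.
- **Making the conclusion depend on category 1 would be a poor remedy.** With a 57% chance of passing when the arms are equal, it would be an underpowered gate. This stands, and the fix avoids it.

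What remains is the gap between label and measure, and the inconsistency over who is asked.

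**Conclusion.** The point holds in a limited form. The outcome is labelled as wearing but includes children who are not wearing and only have their spectacles at school. A shift from wearing to carrying in the ready-made arm could therefore hide a deficit in observed wear. Under the assumed 15-point deficit with 230 per arm, the chance of declaring non-inferiority with a 95% interval runs from 0.765 down to 0.001 as the share of displaced children who carry falls from all to none. These figures rest on invented category rates and a normal approximation. They show that masking is possible, not that it is likely, and the true size and direction are unknown.

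Separately, the Primary outcome section restricts the reason question to categories 3 and 4, while the Additional analyses and Harm sections are not clearly restricted. Followed as the first section is written, symptoms that lead a child to carry but not wear may go unrecorded. The documents do not establish that such children are certainly missed.

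**What to change.** 1. Keep the primary definition. In results and conclusions, describe it as children who wore their spectacles or had them at school, not as wear alone.
2. Report all four categories by arm, and the category 1 risk difference with its 95% interval, as a supportive analysis that does not gate the conclusion. The categories are part of the assessment already, so this needs only analysis time. The drawback is imprecision, about ±9 points at an assumed 50% wear with 230 per arm.
3. Reconcile the Primary outcome, Additional analyses and Harm sections so that every child not wearing at the visit (categories 2 to 4) is offered the existing reason question, where follow-up is still open. This adds one question by the same field worker, plus any re-refraction that follows under the Harm section; the sections must also agree on which children that provision reaches. Recruitment ended on 31 July 2015, so it may be too late for some or all children. If so, state the limitation.
4. Report each reason by arm with all randomised children as the denominator. Comparing reasons only among non-wearers conditions on a post-randomisation outcome that may itself differ between arms. This costs nothing beyond the tabulation.

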### Data management

All field staff have undergone rigorous training, including inter-observer agreement studies for visual acuity measurement and refraction, and instruction on how to record data.

Two password protected databases have been created in Epidata and Excel, one for the primary outcome data and the other for all other data. Consistency and range checks have been built in. Data are double entered by the lead investigator as soon as possible after recruitment to monitor recruitment. During the trial all data recording forms are kept in a locked cupboard or filing cabinet in Sankara Eye Hospital and photocopies made and transferred to London for data cleaning, where they are again stored in a locked filing cabinet.

### Data analyses

Analysis will be in the groups to which the children were randomly allocated. We expect all children will have been given the correct spectacles. The randomisation code will only be broken once the analysis has been completed. We do not plan any subgroup analysis.

#### Comparability of the intervention and comparator groups

To assess comparability of the two groups, characteristics of children in the intervention and comparator arms will be compared by age, gender, degree of uncorrected refractive errors, presenting visual acuity in the better eye, peri-urban/urban school and whether they previously wore spectacles which required replacement.

#### Primary analysis

The proportion of children wearing or having their spectacles with them at school at 3 to 4 months will be compared between the intervention and comparator arms, using the risk difference with 95 % confidence intervals.

We will also calculate and present the risk ratio with 95 % confidence intervals.

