The prevalence of uncorrected refractive errors in children varies by country and by urban/rural location, for example, in India [2–4]. In one study in rural India, 4.1 % of children aged 7–15 years were myopic, and 61 % of visual impairment was due to uncorrected refractive errors [2]. In an urban Indian setting 7.4 % of children aged 5–15 years were myopic and 82 % of visual impairment was due to uncorrected refractive errors. In both studies older children had a higher prevalence of uncorrected refractive error than younger children [4]. Global estimates indicate that 13 million children have visual impairment due to uncorrected refractive errors [5]. A recent study in China provides evidence of what might be anticipated, that academic performance improves with correction of refractive error in children [6]. Studies have also highlighted that correcting refractive error is highly cost effective [7] and improves visual function and quality of life. These findings add impetus to the need for the inclusion of eye health into school health initiatives, which are being supported and scaled up by Ministries of Health and Education, the World Bank, WHO, UNESCO, UNICEF and the Partnership for Child Development. India has had a programme to detect and treat uncorrected refractive errors in school children since 1994 [8].

Approaches being used to detect and correct uncorrected refractive errors in children are not standardised, and spectacle wearing rates can be very low in all settings [5]. For example, in Native American students in the USA, only 32 % of children given two pairs of free spectacles wore their spectacles [9]. Similar findings have been reported from rural areas near Delhi where only 29.4 % of children wore their spectacles [10]. Spectacle wear is higher in children with more severe uncorrected refractive errors [9] and in girls [11]. In another study in India only 30 % of children dispensed spectacles were wearing them at 6–12 months. Spectacle wearing was higher amongst girls, those with higher refractive errors and poor uncorrected visual acuity, and those whose fathers were better educated [12].

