### Sample size calculation

Parameters used in the sample size calculation include a significance level of 0.05, 95 % confidence interval, 90 % power and 1:1 allocation. The trial is powered to detect a non-inferiority margin (∆) of 10 %. No increase has been added for loss to follow-up, as all eligible children present on the day of the visit are being recruited, and high response rates are anticipated based on previous experience. Calculations, which were one sided, were performed using a web-based sample size calculation programme (Sealed Envelope, https://www.sealedenvelope.com/power/binary-noninferior/, accessed 31 October 2014). A sample of 240–260 eligible children will be required in each arm of the trial. The prevalence of uncorrected refractive errors in the earlier study in Bangalore was 4 %. Assuming approximately a third would not be eligible for ready-made spectacles, the effective prevalence would be 2.6 %; therefore, 20,000 children in 200 schools would need to be screened.

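### The primary risk difference reads as unadjusted and so gives up a modest amount of precision that baseline data already collected could recover

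*Protocol article*

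**What the plan says.** The Primary analysis section states that the proportions wearing their spectacles, or having them at school, "will be compared between the intervention and comparator arms, using the risk difference with 95 % confidence intervals"; a risk ratio is also to be presented. No covariate or stratum is named, and the section does not say that adjustment is ruled out.

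Other sections bear on this:

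- **Randomisation:** "The random allocation has been stratified by school", with variable block sizes.
- **Background:** in an earlier Indian study, "Spectacle wearing was higher amongst girls, those with higher refractive errors and poor uncorrected visual acuity". The same section says that increasing myopia independently predicted wear in a Tanzanian trial, and that wearers were more myopic than non-wearers in an earlier Bangalore study (p = 0.001).
- **Comparability of the intervention and comparator groups:** the arms will be compared on age, sex, refractive error, presenting acuity in the better eye, school location and previous spectacle wear. No analytic consequence is attached to an imbalance.
- **Additional analyses:** a multivariable logistic model uses "gender, age, degree of uncorrected refractive error in the better seeing eye, previously wore spectacles" and parental wear, but only to study predictors.
- **Sample size calculation:** "a significance level of 0.05", one-sided, "90 % power and 1:1 allocation", a 10% margin and 240–260 children per arm.
- **Trial status:** recruitment closed with 460 children.

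**The concern.** The authors name covariates where they intend to model, and they name none for the primary comparison. The primary estimate therefore appears to leave unused the variables that their own Background section links to the outcome. Adjusting a risk difference for baseline variables that predict the outcome narrows its interval without recruiting anyone.

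The width of that interval matters here. Non-inferiority presumably turns on whether its lower limit clears −10 points, and the Cost savings section makes the economic analysis conditional on that result. Recruitment also closed 4–12% short of the stated requirement (460/480 = 0.958; 460/520 = 0.885). If adjustment is not fixed in advance, an imbalance found in the baseline comparison could prompt an adjustment chosen after seeing the data.

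**Working it through.** **Inputs from the protocol.** Margin 0.10; power 90%; alpha 0.05 one-sided for the sample size; a 95% interval for the analysis; 240–260 per arm required; 460 recruited, so about 230 per arm; 200 schools planned.

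**Inputs not in the protocol (assumed).** The wear rate p behind the sample size is not stated. The Background section cites rates from about 29% to 52%. The share of outcome variance explained by baseline covariates, R², is also not given and is taken as 0.05–0.15. Arms are taken as equal, with no true difference.

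**Step 1: the plan's own figure.** With n per arm = (z₁₋α + z₀.₉₀)² × 2p(1−p) / 0.10² and one-sided alpha 0.05, (1.645 + 1.282)² ≈ 8.564.

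- p = 0.82: 8.564 × 0.2952 / 0.01 = 253
- p = 0.81: 264; p = 0.83: 242
- p = 0.30: 8.564 × 0.42 / 0.01 = 360
- p = 0.50: 429

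So 240–260 per arm corresponds to wear of about 81–83% (or, by symmetry, 17–19%). It cannot be confirmed, because the assumed rate is missing. The check below therefore spans 30%, 50% and 82%.

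**Step 2: effect on precision.** Adjustment multiplies the variance by about (1 − R²).

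| R² | Standard error multiplied by √(1−R²) | Reduction | 460 children act like 460/(1−R²) |
|---|---|---|---|
| 0.05 | 0.975 | 2.5% | 484 |
| 0.10 | 0.949 | 5.1% | 511 |
| 0.15 | 0.922 | 7.8% | 541 |

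**Step 3: effect on power.** Judged by a two-sided 95% interval with 230 per arm, power = Φ(0.10 / √[(1−R²) × 2p(1−p)/230] − 1.96). For p = 0.30 and R² = 0, √(0.42/230) = 0.0427 and Φ(2.340 − 1.96) = 0.648.

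| Wear | Unadjusted | R² = 0.05 | R² = 0.10 | R² = 0.15 |
|---|---|---|---|---|
| 30% | 64.8% | 67.0% | 69.4% | 71.8% |
| 50% | 57.3% | 59.5% | 61.8% | 64.3% |
| 82% | 79.7% | 81.7% | 83.7% | 85.7% |

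The gain is 2.0–7.0 points. Reaching 90% by adjustment alone would need R² of about 0.26 at 82% wear and about 0.56 at 50%.

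**Step 4: simulation.** 460 children in 200 schools, allocation blocked within school, 1,500 replicates per scenario, wear 50% or 82%. Assumed effects were log-odds 0.5–0.8 per SD of refractive error and 0.4–0.5 for sex, with and without a school effect.

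- Adjustment raised power by about 1–6 points (for example, from 56.7% to 61.1% and from 79.8% to 82.9%).
- With no predictive covariates, power was essentially unchanged (differences of −0.1 to +0.6 points).
- The unadjusted 95% interval that ignored school covered the true value in 94.7–95.7% of replicates.
- A Mantel–Haenszel risk difference stratified by school had a standard error about 7–11% larger than the crude one. There are about 460/200 = 2.3 children per school, and about 14% of children were in schools where only one arm appeared.

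**The case against.** The strongest objection is that nothing here is an error. In an individually randomised trial the crude risk difference is valid, its interval already allows for chance imbalance, and it matches both the margin and the two-proportion sample size. Covariates are often left to a statistical analysis plan, which is not shown. All of this stands, and it limits the point to efficiency and pre-specification. The point survives because the article does state its primary estimator and does name covariates elsewhere.

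A reader might infer two stronger claims, and neither is supported.

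- **That the predictors are strong.** The Background section gives directions of association and no usable effect size. Its one local figure is internally inconsistent: non-wearers have a mean of −2.50 D but a stated range of −0.75 to −2.25 D. The associations also come from children not selected by this trial's criteria, and the acuity association concerns uncorrected acuity, whereas this trial's listed baseline variable is presenting acuity.
- **That stratifying by school makes the crude standard error wrong.** Both arms are allocated within schools, so shared teachers and peers do not inflate the variance of the difference as they would under cluster randomisation. The simulated coverage shows no harm, and stratifying the analysis by school loses precision.

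It is also fair to say that changing a published primary estimator after recruitment has closed needs a stated justification.

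**Conclusion.** The point holds as a modest and inexpensive improvement. Read naturally, the primary analysis is crude, and it leaves unused baseline variables that the protocol itself associates with wear. The size rests on the assumed R² of 0.05–0.15, on equal arms and on no true difference; if the covariates predict little in this population, the gain is close to nil.

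A reader might also infer that adjustment would repair the trial's power. It would not. The larger causes are the unstated wear rate, one-sided 0.05 planning set against a 95% interval, and the recruitment shortfall. Adjustment recovers only part of what is lost.

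**What to change.** Before the randomisation code is broken, and preferably before the outcome database is merged with the other data, record a dated covariate list: refractive error and presenting acuity in the better eye, sex, age, previous spectacle wear and urban/peri-urban school. Fit a logistic model with arm and these covariates, standardise it to a marginal risk difference, and judge its robust 95% interval against −10 points as the primary analysis. Report the crude risk difference as a sensitivity analysis. Do not use school fixed effects or a school-stratified Mantel–Haenszel estimate. The figure of about two children per school assumes the planned 200 schools, since the actual number is not given.

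The scale and margin are unchanged and no new data are needed. The cost is a revised analysis section and a short, dated justification. If outcomes by arm have already been seen, keep the crude difference as primary and present the adjusted one as supportive.
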